## Introduction

Burns are one of the most common types of trauma worldwide, causing significant disability [1, 2]. Today, acute burn care in high- and middle-income countries has improved to the point where the focus has shifted from survival as main outcome to outcomes like quality of life, leaving room to broaden our view to other challenges [3]. One of these challenges is the timing of surgery. The severity of a burn, determined primarily by total body surface area (TBSA) and depth of the injury, influences reparative healing potential, and is a primary indicator of the need for surgery [4–6]. For deep partial-thickness burns, currently no consensus regarding the optimal treatment has been reached, which remains a topic of debate [7]. Contrary to superficial partial-thickness burns and full-thickness burns, where the optimal treatment is evident. Superficial partial-thickness burns affect the epidermal and upper dermal layers of the skin, heal within 14 days and do not require surgery [8]. Full-thickness burns fully penetrate all layers of the skin into the subcutis. No spontaneous healing is expected and excision and grafting are always indicated [8–11].

The healing potential of deep partial-thickness burns varies with the longer time to healing being associated with increased scar risk. Two main treatment strategies are currently applied in high- and middle-income countries: 1) conservative treatment with delayed excision and grafting if needed; 2) early excision and grafting. Conservative treatment involves applying dressings and topical antimicrobial and antiseptic agents to the burn, after which spontaneous healing is awaited. If the remaining defects do not heal spontaneously within 14 to 21 days, the burn specialist can decide to perform excision and grafting. In case of early surgery, excision and grafting of the burn is performed within the first week to ten days post-burn [9].

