### Procedures

#### Conservative treatment with delayed excision and grafting if needed

Initial conservative treatment is one of the strategies used in daily clinical practice to treat deep partial-thickness burns. Patients receive conservative treatment involving the application of dressings and antimicrobial agents. These include silver sulfadiazine (Flammazine®), cerium nitrate-silver sulfadiazine (Flammacerium®), enzymatic hydrated alginate polymers (Flaminal®), or other agents and dressings according to the local protocol of the burn centre. If wound healing is not achieved after 14 to 21 days, excision and grafting of the residual defects can be performed. This is decided based on the expert opinion of the burn specialist and in consultation with the patient.

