### Secondary outcomes

#### Clinical outcomes

Time to wound healing of study area(s): this is defined as the number of days between burn injury and re-epithelialisation of >95% of the wound surface. Progression of re-epithelialisation is assessed by an experienced burn specialist and reported after every wound inspection.

Wound infection of study area(s): the attending physician will document whether a wound infection has occurred, based on inflammation characteristics (rubor, dolor, calor, tumor, functio laesa) in combination with a positive wound culture.

As of 2009, patient and clinical characteristics are prospectively registered in the Dutch Burn Repository (DBR) R3 in the three Dutch burn centres. Clinical outcomes that will be obtained from DBR R3 are mortality (during admission), time to first excision and grafting, length of hospital stay, length of ICU stay, readmission, reoperation, blood transfusion requirements, wound complications (e.g. graft failure), sepsis, shock, reconstructive surgery, number and timing of outpatient visits. To assess the amount of clinical topical wound treatments, the length of hospital stay will be used as a proxy.

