### Statistical analysis

For the statistical analysis descriptive statistics will be used. All parameters will be tested for normality. Depending on the distribution of the data, a mean and standard deviation (normal) or a median and interquartile range (skewed) will be displayed. Differences between the two treatment strategies for the primary outcome measure scar quality and other outcomes will be analysed using two-sided T-test (normally distributed continuous data) or Mann-Whitney U-test (skewed continuous data), and two-sided Chi-square test or Fisher’s exact test (categorical data). Differences between groups in time to event outcomes (i.e. time to surgical intervention and time to wound healing) will be analysed using Kaplan-Meier regression. To correct for the possible influence of patient, burn, and burn centre characteristics on the results, multivariate linear regression (continuous data), multilevel logistic regression (categorical data), and Cox regression (time to event data) will be used. If possible, exploratory analyses will be done on the 10–14 day surgery group. Data analysis will be performed using IBM Statistical Package for the Social Sciences (SPSS) version 26 (SPSS, Chicago, IL, USA) and Python (Python Software Foundation, Delaware, USA).

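### Time to surgical intervention is assigned to Kaplan-Meier although healing without surgery is a competing event; if patients are censored at healing, the probability of delayed grafting will be overstated

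*Protocol article*

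**What the plan says.** The protocol article's Statistical analysis section gives one curve method for two outcomes: "Differences between groups in time to event outcomes (i.e. time to surgical intervention and time to wound healing) will be analysed using Kaplan-Meier regression". For adjusted analyses it adds that "Cox regression (time to event data) will be used". It names no competing-risk method.

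The surgical outcome is listed under Clinical outcomes as "time to first excision and grafting" and is taken from the burn registry. Time to wound healing of the study area is a separate outcome in the same section: "this is defined as the number of days between burn injury and re-epithelialisation of >95% of the wound surface". Death during admission is also listed there.

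The Introduction describes conservative treatment as dressings and topical agents, "after which spontaneous healing is awaited". The Procedures section then says of that strategy: "If wound healing is not achieved after 14 to 21 days, excision and grafting of the residual defects can be performed". The Criteria section defines the target wounds by a healing potential of about 14 to 21 days.

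**The concern.** Kaplan-Meier estimates the probability of an event on the assumption that a censored patient has the same future chance of it as those still under observation. In the conservative strategy, a wound that has healed has essentially no remaining chance of being grafted. Healing is also the intended course, and it is expected in the same two to three weeks in which delayed surgery becomes possible. It is therefore likely to be a frequent competing event.

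If healed patients leave the risk set as censored, the estimator in effect gives them the later grafting risk of patients whose wounds stayed open. One minus Kaplan-Meier is then no longer the proportion who have surgery. This is so within the conservative group alone, whatever comparator is used.

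The Discussion says the results will feed a decision aid and a cost-effectiveness study. Any error of this kind runs one way: conservative treatment would look more likely to end in surgery than it is.

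**Working it through.** **The plan's own figures.** The article states no probability of delayed grafting, so there is nothing to reproduce. Its only relevant number is the expected maximum of 204 patients in 18 months, or 204 / 2 = 102 per nine-month period if recruitment is even. All healing and surgery rates below are assumptions.

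**1. Closed form.** Suppose the hazards of grafting and of healing stay in constant ratio. Let *p* be the share of wound endpoints that are grafts, and *F* the fraction of patients who have reached either endpoint.

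- True cumulative incidence of surgery = *p* × *F*
- 1 − Kaplan-Meier with healing censored = 1 − (1 − *F*)^*p*

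For *p* = 0.3 and *F* = 0.95: 0.3 × 0.95 = 28.5%, against 1 − 0.05^0.3 = 59.3%.

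| *p* (*F* = 0.95) | True | 1 − KM, censored at healing | Gap (points) |
|---|---|---|---|
| 0.1 | 9.5% | 25.9% | 16.4 |
| 0.2 | 19.0% | 45.1% | 26.1 |
| 0.3 | 28.5% | 59.3% | 30.8 |
| 0.5 | 47.5% | 77.6% | 30.1 |
| 0.7 | 66.5% | 87.7% | 21.2 |

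**2. Simulation with a surgery window.** There were 102 patients and 400 runs per scenario. Healing day is normal. A stated share of patients are candidates for surgery on a day drawn evenly from the window, and are operated on if still unhealed. Results are read at day 42.

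| Healing mean (SD), days | Surgery window; share | True | 1 − KM, censored at healing | 1 − KM, healed kept at risk |
|---|---|---|---|---|
| 17.5 (3.5) | 14–21; all | 49.6% | 92.1% | 49.6% |
| 17.5 (3.5) | 14–21; 50% | 25.0% | 42.3% | 25.0% |
| 20 (5) | 14–21; 50% | 33.6% | 45.9% | 33.6% |
| 17.5 (3.5) | 18–25; 80% | 13.7% | 58.2% | 13.7% |
| 17.5 (3.5) | 11–14; 40% | 36.7% | 38.8% | 36.7% |

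With censoring at healing, the gap runs from 38.8 − 36.7 = 2.1 points, where surgery mostly precedes healing, to 58.2 − 13.7 = 44.5 points, where it mostly follows.

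**3. Simulation with a daily surgery hazard.** There were 200,000 patients per scenario. Healing day is normal with SD 4, and surgery occurs from day 14 in unhealed wounds at 5%, 10% or 20% per day. Each cell gives the true proportion by day 28 against 1 − KM censored at healing.

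| Healing mean | 5% per day | 10% per day | 20% per day |
|---|---|---|---|
| 17 | 15.4% v 40.9% | 27.1% v 66.6% | 43.4% v 88.8% |
| 18 | 18.8% v 43.1% | 32.7% v 66.9% | 50.9% v 90.7% |
| 20 | 25.5% v 44.4% | 43.3% v 70.1% | 64.9% v 92.2% |

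The gaps run from 44.4 − 25.5 = 18.9 to 88.8 − 43.4 = 45.4 points at day 28. At day 21 they run from 7 to 32 points.

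**4. The harmless coding.** If healed patients stay at risk to the end of follow-up, nobody is censored before the time of interest. Kaplan-Meier then reduces to the simple proportion without surgery, as the last column in step 2 shows. Only the handling of deaths is left.

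**The case against.** The strongest objection is that the article never says patients are censored at healing. Follow-up is 12 months, and the surgery date comes from the registry while healing is recorded separately, so a patient never operated on could equally be carried to the end of follow-up. A censoring rule may well sit in an analysis plan that is not shown, and its absence here is no fault. This stands. A reader might infer that the plan will certainly overstate the probability of delayed grafting; the article does not support that. What remains is that it fixes an estimator which gives the right probability only under one coding, for an outcome with an evident competing event.

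Four further points stand in part:

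- **Use of the curve.** Kaplan-Meier is named for group differences, and nothing says that a grafting probability will be read from it. A reader might infer that this is a central figure of the decision aid, but the article says only that the study's results will feed one.
- **Cox regression.** With healing censored, Cox regression is a valid comparison of cause-specific hazards. It would mislead only if read as an effect on the chance of surgery, and the article does not read it so.
- **Size.** The daily-hazard scenarios allow no surgery before day 14, yet the Statistical analysis section mentions a 10–14 day surgery group. When surgery mostly precedes healing, the gap is about 2 points. The day-28 estimates also rest on very few patients still at risk (0.02% to 1.5%, at most about 2 of 102).
- **Unit.** Healing is defined for the study area, but the registry surgery outcome is not so labelled. Up to two burns per patient are followed, and mixed-depth burns are eligible. Healing of a study area therefore need not end the patient's risk of surgery elsewhere, and the remedy has to deal with this.

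**Conclusion.** The concern holds in conditional form. Under the article's own description of conservative treatment, healing without surgery is a competing event for time to surgery, and so is death during admission. If patients are censored at healing, or at discharge after healing, 1 minus Kaplan-Meier will overstate the probability of delayed grafting by about 2 to 45 percentage points in the scenarios examined. If healed patients stay at risk to the end of follow-up, the overstatement is zero apart from deaths. These sizes rest on assumed healing and surgery rates.

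The consequence is limited to one secondary outcome. Groups are formed by treatment received, and the early group is defined by surgery within about ten days, so a between-group comparison of time to surgery largely restates the grouping. The curve is informative mainly within the conservative group or by calendar period. Time to wound healing is not affected in the same way, because it is dated from injury whether or not the wound is grafted.

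**What to change.** - For time to surgical intervention, replace Kaplan-Meier with the cumulative incidence of surgery (Aalen-Johansen), with healing without surgery and death as competing events. Present it mainly within the conservative group or by calendar period.
- Define surgery and healing on the same unit: either the study area, or the patient with all burns healed.
- Label any Cox result for surgery as a cause-specific hazard ratio, and do not interpret it as an effect on the chance of surgery. If such an effect is wanted, Gray's test or Fine-Gray regression provides it.
- Keep Kaplan-Meier and Cox for time to wound healing, with grafted wounds followed to healing.

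The cost is analysis wording. Study-area healing and first surgery are already dated, and Python, which the plan names, can do the analysis. The unit needs some care: a study-area analysis needs surgery dates tied to the area, and a patient-level analysis needs a date when all burns have healed. Cumulative incidence agrees with Kaplan-Meier where the coding is harmless and corrects it where it is not, so the reported probability of delayed surgery will be the same or lower.

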## Materials and methods

### Study design

A multicentre prospective study with a 12-month follow-up period will be conducted in the three Dutch burn centres: Maasstad Hospital Rotterdam, Red Cross Hospital Beverwijk, and Martini Hospital Groningen. Patients with deep partial-thickness burns, scanned as yellow by Laser Doppler Imaging (LDI), will be monitored during 18 months; two nine-month periods with either therapy as the treatment of choice in one of the periods. This time period was chosen based on expected numbers and project logistics, such as staffing. Standard care in the Netherlands for deep partial-thickness burns is predominantly conservative treatment with delayed excision and grafting if needed. However, early excision and grafting is applied if deemed more appropriate for a specific patient. The first nine-month period (July 15^th^ 2022 to April 14^th^ 2023) this strategy is followed. In the following nine-month period (April 15^th^ 2023 to January 14^th^ 2024) clinical practice will be changed: early excision and grafting will be the primary treatment. However, in specific cases e.g. based on clinical expertise, conservative treatment can be applied. Depending on the received treatment, patients will be categorized as either the conservative treatment group with delayed excision and grafting if needed, or the early excision and grafting group.

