### Participants

#### Selection

Neither, randomisation nor blinding will take place. The used treatment strategy determines to which group the patient is assigned. The first group represents conservative treatment with delayed excision and grafting if needed, the second group represents early excision and grafting. If a patient is eligible for the study, a member of the research team will provide information about the study. The patient is asked for consent to take additional measurements 12 months after discharge. After reflection time and written informed consent, the patient is included.

Anyone using the protocol must consider the ethical implications of the timing of surgery in their own practice setting. To ensure patient safety, the attending physician is justified in deciding not to start or discontinue treatment from the allocated treatment, based on sound medical grounds and after consulting with the health care team. Deviation from the assigned treatment should be rare, and the reason must be thoroughly documented.

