#### Early excision and grafting

Patients initially receive abovementioned topical treatment, followed by excision and grafting of the burn in the first week to ten days post-burn.

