#### Patient and treatment characteristics

Demographics, burn characteristics, and treatment characteristics will be obtained from DBR R3.

Demographics: age, gender, medical history, referral, burn centre. Burn characteristics: TBSA, date of burn injury, burn localisation, burn aetiology, inhalation injury. Treatment characteristics: date of initial surgical intervention and thereby time till first surgical intervention (in days), admission on Intensive Care Unit (ICU), ventilation, topical wound treatments, and wound debridement method, type of grafting, other surgical interventions if applicable.

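### The between-group test of time to surgery restates how the groups are defined, and the time-to-healing comparison starts the clock before group membership is settled

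*Protocol article*

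**What the plan says.** All references are to the protocol article.

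- **Grouping.** Study design: "Depending on the received treatment, patients will be categorized as either the conservative treatment group with delayed excision and grafting if needed", or as the early excision and grafting group. The Selection section agrees: "The used treatment strategy determines to which group the patient is assigned".
- **Early group.** Topical treatment "followed by excision and grafting of the burn in the first week to ten days post-burn".
- **Conservative group.** Dressings and topical agents first, then: "If wound healing is not achieved after 14 to 21 days, excision and grafting of the residual defects can be performed".
- **Clock for healing.** Clinical outcomes: "this is defined as the number of days between burn injury and re-epithelialisation of >95% of the wound surface".
- **Analysis.** Statistical analysis: "Differences between groups in time to event outcomes (i.e. time to surgical intervention and time to wound healing) will be analysed using Kaplan-Meier regression". For adjustment on patient, burn and centre characteristics, "Cox regression (time to event data) will be used". The article mentions no landmark, time-dependent surgery term or comparison by calendar period.

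**The concern.** The two time-to-event comparisons have different faults with the same source: group membership depends on something that happens after the clock starts.

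For time to surgery, the outcome is the variable that separates the groups. A significant result is guaranteed and says nothing about the strategies.

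For time to healing, a patient must still be unhealed on the day of surgery to enter the early group. Someone meant for early surgery who heals first, or for whom surgery is withheld, is counted as conservative together with all the time since the burn. Adjusting for characteristics known at baseline does not undo a classification made later.

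Healing time is the first secondary clinical outcome listed. The Discussion says the results will go into a cost-effectiveness study and a decision aid for patients, so a distorted healing comparison would travel further than this study.

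**Working it through.** The article gives no figure for these outcomes, so there is nothing to reproduce. The check is structural, followed by simulation under no treatment effect.

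**1. Time to surgery**

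Let S be the post-burn day of excision and grafting, and let a patient be early if S ≤ 10.

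- P(S ≤ 10 | early) = 1
- P(S ≤ 10 | conservative) = 0

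At day ten the two curves are at opposite ends whatever the data are. With 204 patients, 60% operated on at a day drawn uniformly from 3 to 28, and 300 replicates, separation was complete in every replicate. No assumption about healing is involved. Moving the cut-off from ten days to a week changes nothing.

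**2. Time to healing**

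Let H be days from burn to healing and S the planned day of early surgery. A patient is received-early only if planned early and H > S. Hence P(H ≤ S | early) = 0, and planned patients with H ≤ S move to conservative.

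*From the article:* at most 204 patients; healing potential of about 14 to 21 days for yellow areas; surgery by about day ten; clock from the burn.

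*Assumed:* H lognormal with median m and log-SD s; half of patients planned early, independently of H; S uniform on days 5 to 10; surgery has no effect on H; no censoring; 1,000 replicates; one-covariate Cox model.

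Share healed by day ten = Φ(ln(10/m)/s). For m = 17.5 and s = 0.40: ln(10/17.5) = −0.560; −0.560/0.40 = −1.40; Φ(−1.40) = 0.081.

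| m | s | Healed by day 10 | Planned-early moved to conservative | HR, as received | Rejection at 5% | HR, by period |
|---|---|---|---|---|---|---|
| 17.5 | 0.11 | 0.0% | 0.0% | 1.01 | 6.1% | 1.01 |
| 17.5 | 0.25 | 1.3% | 0.2% | 0.99 | 5.4% | 1.00 |
| 17.5 | 0.40 | 8.1% | 2.5% | 0.95 | 7.5% | 1.00 |
| 17.5 | 0.60 | 17.5% | 8.4% | 0.85 | 20.6% | 1.00 |
| 14 | 0.11 | 0.1% | 0.0% | 1.00 | 4.6% | 1.00 |
| 14 | 0.25 | 8.9% | 1.9% | 0.96 | 6.4% | 1.00 |
| 14 | 0.40 | 20.0% | 7.4% | 0.87 | 15.7% | 1.00 |
| 14 | 0.60 | 28.7% | 15.5% | 0.75 | 51.9% | 1.00 |

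An HR below 1 means early surgery looks slower to heal. A separate run with S uniform on days 3 to 10 gave 0.98 (m = 17, s = 0.35; 6% healed by day ten), 0.92 (m = 17, s = 0.50; about 15%) and 0.85 (m = 14, s = 0.50; 25%). The HR is not a function of the healed share alone, so these figures give a range. The by-period column assumes no secular trend between the two nine-month periods.

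**3. Why a landmark or time-dependent term addresses this part**

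At a day-ten landmark every retained patient has H > 10 ≥ S, so planned and received membership coincide in this set-up and nobody is reclassified. With a time-dependent term, days before surgery, and any healing in them, count as not yet operated. Neither corrects for how patients were chosen for surgery.

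**The case against.** The strongest reply concerns size. Study areas must be yellow, or have a demarcated, predominantly yellow part of at least 25 cm², with healing potential of about 14 to 21 days. The article puts LDI accuracy above 95%. The lognormals in the separate run place only 44% (m = 17, s = 0.35), 31% (17, 0.50) and 29% (14, 0.50) of healing times in days 14 to 21. The last has half of all areas healed before day 14, which is the article's red category. Mixed red and yellow burns are a weak justification, because healing is measured on the study area. All this stands. For the population described, the immortal-time part may be close to nil.

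Direction is also open. Fast healers moving to conservative make early surgery look slower. Patients withheld from surgery because they became unfit may heal slowly, which works the other way. A reader might infer that the healing hazard ratio is biased against early excision as a matter of fact. The article does not support that.

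A reader might also point to slow healers being chosen for surgery. When the simulated log-odds of surgery rose by 0.5 to 1 per SD of slowness, the HR was 0.74 to 0.55 with almost no healing before day ten. That is confounding by indication, a different defect, and it is not evidence of immortal time.

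The article does not say that group enters the Cox model as a fixed covariate, and an analysis plan could specify otherwise. The Selection section also speaks of allocated treatment and rare deviation, which hints at grouping by strategy. The explicit rule in Study design is nevertheless treatment received. Under that rule, rare deviation shrinks the healing problem but leaves the time-to-surgery test circular. Calling Kaplan-Meier a regression is only loose wording: Cox regression is named next and does compare groups.

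**Conclusion.** **Time to surgery: wrong as written.** The comparison is circular under the stated grouping rule, with no distributional assumption needed.

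**Time to healing: a cheap improvement.** The mechanism follows from the burn-date clock and grouping by treatment received, but its size is not fixed by the article. With at most about 1% of areas healed by day ten, the null HR is 0.99 to 1.01. At about 8% to 9% it is 0.95 to 0.96. At about 15% to 25% it is about 0.85 to 0.92. The value of 0.75 needs nearly 29% healed by day ten, which sits badly with the eligibility criteria. These values rest on assumed lognormal healing, half of patients planned early, and choice of surgery unrelated to healing. The sign is secure only if early healing is the sole route out of the early group.

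**What to change.** 1. Delete the between-group test of time to surgery. Report its distribution by period, as a description of how far the change of strategy was taken up.
2. For the as-received healing comparison, keep the clock at the burn and enter early surgery as a time-dependent covariate, or use a day-ten landmark among patients alive and unhealed. State which.
3. Add a comparison of healing by period of injury as a sensitivity analysis. State that it assumes no secular trend and that permitted crossover dilutes it. It answers a different question, the effect of the strategy in force, so it should not replace item 2.

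The cost is analysis wording only. Dates of burn and first surgery are already collected, and the period boundaries are fixed in Study design. The landmark loses patients healed before day ten: few if healing follows the LDI range, more otherwise. That number should be reported, since it also shows how much the issue mattered.

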#### Criteria

Adult (≥18 years) patients with acute thermal burns who are admitted for at least 24 hours or scheduled for surgery are eligible for this study, when the criteria listed below are met.

Inclusion criteria:

Burns with a size of >2.5 centimetres diameter;LDI scan indicating:
Deep partial-thickness burn: yellow wound area on LDI with healing potential between 14 and 21 days, or;Mixed superficial and deep partial-thickness burn: mixed red and yellow wound area on LDI, with a demarcated predominantly yellow area of at least 25cm^2^, or;Mixed full-thickness and deep partial-thickness burn: mixed blue and yellow wound area on LDI, with a demarcated predominantly yellow area of at least 25cm^2^.

The colour codes representing the perfusion units (PU) and healing potential are as follows [8, 23]:

Red/pink: PU 441–2500, healing potential within 14 days;Yellow/green: PU 201–440, healing potential about 14 to 21 days;Blue: PU 0–200, healing potential more than 21 days.

Exclusion criteria:

Frostbite injury [24];Burns suitable for primary closure;Patients unable to complete the Patient and Observer Scar Assessment Scale (POSAS) due to language restrictions or legal incompetence.

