### Sample size

No formal sample size calculation was performed for this prospective study. The sample size was assessed using data from DBR R3 (unpublished data, 2019) and a randomized controlled trial on LDI in patients with indeterminate depth burns in Dutch burn centres [37]. Excluding patients with superficial burns and patients with full-thickness burn injuries, and extrapolating the data to three burn centres, the expected sample size is a maximum of 204 patients for the 18-month study period.

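### Time to wound healing: Cox regression is the only adjusted analysis named, although proportional hazards is very unlikely under the two timetables, and the unadjusted method is misnamed

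*Protocol article*

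**What the plan says.** Healing time is a secondary outcome, defined under Clinical outcomes as "the number of days between burn injury and re-epithelialisation of >95% of the wound surface". The clock therefore starts at the injury in both groups.

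Statistical analysis gives two methods for time-to-event outcomes. The group comparison reads: "Differences between groups in time to event outcomes (i.e. time to surgical intervention and time to wound healing) will be analysed using Kaplan-Meier regression". The correction for patient, burn and centre characteristics reads: "multilevel logistic regression (categorical data), and Cox regression (time to event data) will be used". No other adjusted method is named for these outcomes.

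Three other places fix the timetable:
- Criteria gives the yellow/green areas a "healing potential about 14 to 21 days".
- The conservative strategy says: "If wound healing is not achieved after 14 to 21 days, excision and grafting of the residual defects can be performed".
- The early strategy is initial topical treatment "followed by excision and grafting of the burn in the first week to ten days post-burn".

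Patients are grouped by what they received: "Depending on the received treatment, patients will be categorized as either the conservative treatment group".

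**The concern.** There are two separate problems.

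The first is one of wording. Kaplan-Meier estimates a curve. It is not a regression and is not itself a test of a difference, so the unadjusted comparison is not defined as written.

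The second is one of substance. A standard Cox model gives one ratio, taken to be constant over time. Here the treatments act at different times on the same clock. After day 21 the unhealed conservative areas are mainly slow or newly grafted wounds, while the unhealed early areas were grafted at least 11 days before (21 - 10). The ratio of healing rates is then likely to change strongly around days 14 to 21, and one number averages over that change.

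The study is not randomised, so readers will lean on the adjusted result. The Discussion says the results will feed a decision aid and a cost-effectiveness study. Both are better served by days and proportions healed than by a hazard ratio.

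**Working it through.** The article states no hazard ratio, healed proportion or graft-to-closure time, so there is no figure to reproduce. The check asks what a Cox ratio would show under the stated windows.

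**Inputs from the article.** Spontaneous healing on days 14-21 (Criteria); delayed grafting on days 14-21 (conservative strategy); early grafting by day 10 (early strategy); and, from Sample size, "the expected sample size is a maximum of 204 patients for the 18-month study period".

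**Assumptions.** Uniform spread within each window; early surgery on days 5-10; 30% of conservative areas grafted late (range 10-50%); time L from graft to closure, equal in both groups, varied below; 102 per group (204 / 2); no censoring.

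**Step 1: L = 10-16 days, proportion healed by day 21.**
- Early: with surgery on day S, P(unhealed at 21) is the mean of (S - 5)/6 for S uniform on 5-10, which is 2.5/6 = 0.417. So 58% are healed.
- Conservative: late-grafted areas cannot close before day 14 + 10 = 24. So 70% are healed.

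**Step 2: mean days to healing.**
- Early: 7.5 + 13 = 20.5.
- Conservative: 0.70 × 17.5 + 0.30 × (17.5 + 13) = 12.25 + 9.15 = 21.4.
- Early is faster by 0.9 day. The last closure is at day 21 + 16 = 37, so truncation at day 42 changes nothing.

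**Step 3: rate ratios by window, early v conservative (200,000 simulated areas per group).** 0.35 on days 14.5-18, 1.0 on days 18-21, about 21 on days 21-28. The Cox ratio at 102 per group is 1.30 (above 1 means early heals faster). Over 10-50% late grafting it runs from 0.60 to 2.61.

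**Step 4: other closure times.**
- L = 5-10: every estimable window favours early surgery and the Cox ratio is about 4 to 8 over 10-50% late grafting. Healed by day 21: 100% v 53-91%. There is no crossing.
- L = 7-14, 30% grafted late: window ratios 1.2, 1.9 and 11, all above 1. Means: 7.5 + 10.5 = 18.0 v 12.25 + 0.30 × 28 = 20.65 days.
- L = 12-20, 30% grafted late: Cox ratio 1.04, with 20% v 70% healed by day 21. Means: 7.5 + 16 = 23.5 v 12.25 + 0.30 × 33.5 = 22.3 days, so early is 1.2 days slower.

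For closure times from 7-14 to 12-20 days and 10%, 30% or 50% late grafting, the days 21-28 ratio was always above 11, and the days 14.5-18 ratio never exceeded 1.9.

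**Step 5: softer spontaneous healing.** Replace the hard end at day 21 by a log-normal time with median 17.15 days, with L = 10-16 and 30% grafted late.
- Log-SD 0.20: 58% v 59% healed by day 21; late-window ratio 8.5.
- Log-SD 0.25: 58% v 55%; late-window ratio 8.0.

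With L = 12-20, the Cox ratio rises to as much as 1.29 while early surgery remains about 1.1 days slower.

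**Step 6: wider grid.** 60 scenarios: early surgery on days 3-10; 40-80% spontaneous healing; L of 7-14, 10-14, 10-17 or 12-20; early graft failure of 0, 10 or 20%, adding 10-21 days. The Cox ratio and the day-21 proportion disagreed in sign in 14 of 60. A second pass found 10 of 60 clear (ratio outside 0.95-1.05 and day-21 difference over 5 points). With L of 7-14 or 10-14 no clear reversal towards early surgery appeared. Examples at 102 v 102:
- 60% spontaneous, L = 7-14, 10% failure: 82% v 60% healed by day 21, Cox 1.49, 3.1 days faster; no reversal.
- 70% spontaneous, L = 10-17, no failure: 63% v 70%, Cox 1.43, 1.6 days faster; reversed in 82% of simulated trials.
- 60% spontaneous, L = 12-20, no failure: 32% v 60%, Cox 1.63, 1.4 days faster; reversed in 100%.

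A Schoenfeld-residual check rejected proportionality in 11% to 100% of trials, depending on the scenario.

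**The case against.** The strongest reply has four parts.

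1. *The article fixes surgery windows and an expected spontaneous healing window, not when grafted areas close.* This stands. A reader might infer that the design itself makes the hazards non-proportional, or makes them cross. The text supports very unlikely to be proportional, and no more. Crossing disappears with closure at 5-10 days.

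2. *The reversal against day-21 healing needs slow closure and leans on a hard end at day 21.* This largely stands. With log-normal spontaneous healing, the contrast of 58% v 70% shrinks to 58% v 59% or turns to 58% v 55%. The ratio still varies strongly over time, with a late-window value of 8 or more.

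3. *The Cox ratio agrees in direction with mean healing time, so it is incomplete but not misleading.* This holds for closure up to about 10-16 days, but not throughout. At 12-20 days with 30% late grafting, the ratio is 1.04 to 1.29 in favour of early surgery while mean healing is 1.1 to 1.2 days slower.

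4. *The article does not say that a hazard ratio is the sole summary, Kaplan-Meier curves already give unadjusted proportions, and checks of proportionality belong in an analysis plan that is not shown.* This is fair, and the lack of such a check is not held against the article. What remains is that Cox is the only adjusted method it names for this outcome. A data-driven check would also be an unreliable safeguard, since in some scenarios it rejects in only 11% of trials.

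**Conclusion.** The point holds in limited form. The Kaplan-Meier wording is an error that needs correcting whatever is assumed. Cox regression as the only named adjusted analysis of healing time is a poor choice, because a constant ratio is very unlikely under the stated timetable.

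The size and direction of the distortion rest on assumed closure times and an assumed share of late grafting. With fast closure the ratio varies but stays on one side of 1. With closure of about 10-16 days or more it can cross, and the single ratio can then favour early surgery although fewer wounds are healed by day 21. At 12-20 days it can do so although mean healing is slower.

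A reader might go further and conclude that the planned ratio will mislead. The documents do not support that: clear reversals were a minority, 10 of 60 scenarios. Nor is the main conclusion at risk, since the primary outcome is scar quality at 12 months. This is a cheap improvement to a secondary outcome.

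**What to change.** Make two changes in Statistical analysis.

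1. Replace the Kaplan-Meier regression wording with Kaplan-Meier curves and a named test, for both time-to-event outcomes listed there.
2. For time to wound healing, pre-specify as main summaries (i) the covariate-adjusted difference in restricted mean days to healing up to a fixed day, for example day 42, and (ii) covariate-adjusted proportions healed by days 14, 21 and 28. Pseudo-value regression or weighting gives both. Cox regression need not be removed, but should be at most a supporting result.

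The cost is some extra analysis work and a truncation day that has to be chosen and justified in advance. No new data are needed, and the methods are available in Python, which the article already plans to use.
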